## 1.0 Objectives

The goals of this project are to develop deep learning models that can represent patients' clinical trajectories based on text data within electronic health records, and to evaluate the feasibility of incorporating these models into the existing MatchMiner institutional clinical trial matching tool to optimize accrual rates to biomarker-selected therapeutic clinical trials. The study will include an algorithm development and a model implementation component. The algorithm development component will be a mixed retrospective and prospective analysis of medical records data for patients who have undergone OncoPanel genomic testing from 2013-2022. Structured and unstructured data for these patients will be requested using the OncDRS infrastructure, with monthly refreshes requested to include continuously up-to-date records.

The model implementation component will apply these models as new medical records are generated, in order to evaluate the impact on clinical trial accrual of providing information from the Dana-Farber MatchMiner tool to providers and principal investigators when patients appear 'ready' for a clinical trial based on algorithmic predictions. MatchMiner is an established clinical operations tool at DFCI that links OncoPanel data to basic clinical information and clinical trial eligibility criteria to suggest biomarker-selected therapeutic trials for patients.

Our project will itself involve no direct patient contact, no interventions directly upon patients, and no assessment of interventions on health-related patient outcomes; it is a cancer care delivery/clinical operations research study. This proposal therefore does not comprise a therapeutic clinical trial in its own right. The outcomes of our prospective component will be evaluation in the Center for Cancer Therapeutic Innovation; rates of consent to any therapeutic clinical trial; and rates of enrollment in any therapeutic clinical trial during the implementation study. Clinicians will continue to decide whether to approach any patient flagged as a potential therapeutic trial candidate, and informed consent would be obtained for those therapeutic trials in the usual manner. Algorithm development to date has proceeded under protocol 16-360. The current protocol proposes to apply these models to optimize delivery of information from the MatchMiner tool.

The overall study objectives are to:

1. Develop and validate a clinically relevant, dynamic, pre-trained cancer trajectory model by applying deep learning to integrated structured and unstructured EHR data.
2. Apply transfer learning to a pre-trained cancer trajectory model to match patients to clinical trials using EHR data and clinical trial protocols.
3. Pilot the incorporation of cancer trajectory modeling into clinical trial accrual efforts for patients whose tumors have undergone next-generation sequencing.

## 2.0 Background

The U.S. healthcare system has rapidly incorporated electronic health records (EHRs) into routine clinical practice over the last ten years. In oncology, the large volume of data contained within EHRs could constitute a source of 'real-world evidence' to drive research and optimize care delivery. However, most of this information remains untapped. Key oncologic variables, such as

disease histology and stage, often exist in the EHR only in unstructured form. Even when structured data are available, they may capture cancer status only at one point at time, without capturing dynamic shifts in phenotype occurring across the disease trajectory. Without this information, identifying cohorts of patients eligible for research, quality improvement efforts, and clinical trials requires resource-intensive manual medical records review, which may be prohibitive at scale.

Clinical trial enrollment rates among adults with cancer have historically been under 5%. Despite the large population of patients who do not enroll in trials, studies often struggle to reach their accrual goals. A variety of services are in development by government, academia, and industry to improve matching between patients and available trials, but no such frameworks both incorporate unstructured EHR data and are readily available to the public. At Dana-Farber Cancer Institute (DFCI), the MatchMiner tool has been developed to link patients to clinical trials using structured genomic data. However, MatchMiner does not yet contain a mechanism for specifically identifying clinically eligible patients when they most need a new treatment.

Rapid innovation in deep learning techniques may provide novel solutions to these challenges. In recent work, we have found that deep learning classifiers can accurately extract key oncologic outcomes from radiology report text. Deep learning additionally facilitates transfer learning, in which models pre-trained for one purpose can be applied to related problems, using less labeled data than might otherwise be required. It can further readily be applied to classification and prediction problems using sequences of input and multiple types of data. Pre-trained deep learning methods that represent both static (e.g., histology) and dynamic (e.g., cancer progression) oncologic features using a complex array of structured and unstructured EHR data could constitute a transformative technology in support of cohort definition and prediction tasks.

The goals of this proposal are to develop scalable deep learning methods for capturing a patient's cancer status and trajectory using EHR data, and to apply these techniques to build an open framework for improving accrual to clinical trials.

### **3.0 Inclusion and Exclusion Criteria**

The cohort will consist of adults with any type of cancer whose tumors underwent OncoPanel genomic sequencing from 2013-2022. Children will not be included, due to incomplete capture of the EHR data necessary to train machine learning models, given the high proportion of care delivered at Children's Hospital Boston for children with cancer. OncDRS will be utilized to identify all patients and assess for eligibility for this study.

### **4.0 Study-Wide Number of Subjects**

This is a medical record data analysis and health system implementation project using data files from Dana-Farber Cancer Institute (DFCI) and satellite sites. The study type consists of combined retrospective medical record review, *prospective* OncDRS data refreshes, and prospective implementation.

- Retrospective Review Component: The study team ran an aggregate query request in OncDRS as of April 2022 to see how many patients had undergone OncoPanel sequencing by that date. This query resulted in approximately 51,417 patients.

- Prospective Review Component: We will refresh the OncDRS data query/request once a year to capture new cases.

For this project, up to 60,000 records could be pulled for algorithm development and MatchMiner enhancement. We will not exceed 60,000 record reviews without prior IRB approval.

## **5.0 Study-Wide Recruitment Methods**

Not applicable – The cohort for this project is defined as those patients whose tumors have undergone next-generation sequencing either on a research basis under protocols 11-104 or 17-000, or on a clinical basis via Clinical Oncopanel. The current project therefore does not involve direct patient recruitment.

## **6.0 Multi-Site Research**

Not applicable – This is NOT a multi-site research project.

## **7.0 Study Timelines**

Initial algorithm development is complete, and algorithms are being refined based on our prospective pilot. We will continue to pilot delivery of tailored MatchMiner information to disease centers including the Center for Cancer Therapeutic Innovation, the Breast Oncology Center, and the Thoracic Oncology program through 2025. In the second half of 2022, a retrospective data analysis and medical record review will be undertaken to evaluate the sensitivity, specificity, positive predictive value, and negative predictive value of our NLP models for predicting clinical trial consent and enrollment, and to evaluate reasons for non-enrollment in trials. During 2023, we will undertake the prospective component of our intervention, which will evaluate the impact of different strategies for delivering MatchMiner information on clinical trial evaluation, consent, and enrollment rates.

## **8.0 Study Endpoints**

For algorithm development using EHR data, outcomes for model training will include disease progression, defined using a structured manual annotation framework for model training (protocol 16-360); initiation of new systemic therapies; evaluation in the Center for Cancer Therapeutic Innovation; consents to therapeutic clinical trials; enrollments in therapeutic trials; and overall survival.

The primary endpoint that will be assessed by the interventional component of this study is whether each patient with NGS (OncoPanel) data enrolls in any therapeutic clinical trial within one month following the end of the intervention period. Key secondary endpoints will include consultations with the Center for Cancer Therapeutic Innovation and rates of consent to any therapeutic clinical trial during that period.

## **9.0 Procedures Involved**

The algorithm development component of this study has included a medical record analysis project using Dana-Farber Cancer Institute data files and involves no medical procedures or treatments per se. This work is currently underway per protocol 16-360, and it involves analysis of records dating from 1997-2022 for OncoPanel patients for whom genomic testing was ordered

PROTOCOL TITLE: Deep clinical trajectory modeling to optimize accrual to cancer clinical trials

from 2013-2022. These records are used to train machine learning/natural language processing models to predict changes in treatment, prognosis, progression of disease, and sites of metastatic disease using retrospective imaging reports. These models can then be applied prospectively to identify patients who may be appropriate candidates for clinical trials at specific moments in time due to a high propensity to change treatment in the near future.

For the intervention component, there will be two phases.

The first phase of the intervention component will consist of a pilot phase in which our AI algorithms for predicting treatment changes and prognosis are incorporated into the MatchMiner “patients for clinical trials” workflow. Specifically, filters already generated by the MatchMiner team to identify patients who may be candidates for specific clinical trials based on NGS data will be cross-referenced with predictions of new treatment and prognosis that are generated each time a patient has an imaging report generated for cancer reassessment. This combined information will be used to sort the list of filter patients by propensity to change treatment as well as timing of most recent progression and brain metastasis. These sorted MatchMiner lists will then be delivered as spreadsheets to collaborating investigators in the Center for Cancer Therapeutic Innovation, the Breast Oncology Center, and the Thoracic Oncology Program, and qualitative feedback will be solicited regarding steps to improve our modeling and/or delivery of information. Feedback will be collected via a structured SurveyMonkey survey every six months and informally via meetings with these disease centers. These collaborators are co-investigators on our protocol, not research subjects. Survey questions will ask respondents to provide their disease center; role (MD, RN NP/PA, other); estimates of how often they review trial readiness spreadsheets; estimates of the extent to which the readiness spreadsheets have been incorporated into disease center team workflows; estimates of the subjective accuracy of trial readiness predictions; estimates of whether patients have consented to trials or enrolled on trials specifically because of these predictions; feature requests; any ethical concerns; and whether readiness spreadsheets are being used in disease centers for any purposes other than identifying patients for clinical trials (eg maintaining disease center databases, identifying patients who may need palliative care services). CCTI will also review each ‘ready’ patient in our spreadsheets to indicate whether a patient was indeed discussed with the treating clinician for possible referral to CCTI; and if not, why not.

The second phase of the intervention component will consist of a pragmatic, prospective, randomized health care system process implementation study. This is not a clinical trial by the NIH definition, since the outcomes assessed will be operational rather than patient-level behavioral or health-related outcomes.

The intervention procedure for this second phase will be:

- On the study go-live date, which is currently anticipated to be January 2, 2023 but may be adjusted if needed based on technical factors identified during the pilot phase, we will identify all patients with OncoPanel results (who therefore have data accessible through MatchMiner already), who are still alive at that date, whose tumor NGS included any OncoTree code other than leukemia, lymphoma, myeloma, or MDS codes; and who are age 18 or over on that date.

261

262 • Such patients will be randomly divided into three groups; randomization will be  
263 performed at the patient level. For Group 1, MatchMiner will operate as it has previously;  
264 clinicians can use the software to identify potential trials for their patients based on NGS  
265 data, and clinical trial investigators can use it to identify potential patients for their trials.  
266 For Group 2, MatchMiner will continue to operate as before, but additionally, email  
267 notifications containing MatchMiner information will be automatically sent to treating  
268 oncologists each time a patient is clinical trial “ready” (has a predicted probability of  
269 treatment change that falls above the best F1 cutoff threshold for this prediction as  
270 evaluated in the retrospective validation set, also has MatchMiner trial matches for trials  
271 on which the patient has not previously enrolled, and has not triggered a recent  
272 “readiness” email to the treating clinician). For Group 3, MatchMiner will still continue  
273 to operate as before, with NGS-based matches available to all treating oncologists and  
274 trial investigators, and additionally, lists of “ready” patients will be generated based on  
275 AI model results as in Group 2; however, these lists will be manually reviewed by the  
276 study team and cross-referenced with manual medical record review before the  
277 MatchMiner notifications are emailed to treating oncologists. Manual review criteria for  
278 proceeding with each email will include evaluation of whether patients have already been  
279 referred to hospice or are being treated with comfort measures only at the time of the last  
280 imaging report; whether patients have documented performance status of 3-4; and  
281 whether patients are obviously ineligible for all trials provided in the MatchMiner report  
282 as evaluable in the medical record based on trial-specific eligibility criteria. There will be  
283 no direct contact with patients in this study.

284

285 • We have collected preliminary data to inform the randomization and analysis strategy. As  
286 of February 2022, there were 46,097 patients with tumor NGS (OncoPanel) data..  
287 However, this includes both living and deceased patients, patients with hematologic  
288 malignancies who will not be included in this study, and patients not actively following at  
289 DFCI. We therefore examined our AI algorithm development data from 2019 (to exclude  
290 COVID-related variability in trial accrual). We estimate that there were 11,650 patients  
291 who had NGS data and who had any imaging studies from January 1, 2019 through  
292 October 31, 2019. Of these patients, approximately 890 (7.6%) enrolled in a therapeutic  
293 clinical trial between January 1, 2019 and November 30, 2019. If we perform 1:1:1  
294 randomization for all living patients with NGS and given growth in the PROFILE cohort  
295 since 2019, we will therefore have approximately 3800 patients in each group who have  
296 imaging studies during our ten-month intervention period. Stratified randomization will  
297 not be performed, due to the large sample size and heterogeneity in treating disease  
298 centers, treating clinicians, cancer types. Clinicians will be given the opportunity to opt  
299 out of ongoing emails from the study in general, or for individual patients, at any time.  
300 Patients whose clinicians opt out of notifications will remain in their assigned group for  
301 analysis; that is, the primary analysis will follow an intention to treat approach.

302 The primary study outcome will be whether patients enroll on any DFCI therapeutic  
303 clinical trial of an anti-cancer systemic therapy during the intervention follow-up period.  
304 This period will be defined as follows. Beginning in December 2023, total trial

enrollment events across all three study arms will be quantified every two months, without comparing enrollment among arms; the goal of this procedure is to ensure adequate statistical power to compare among arms. Once total trial enrollment reaches 1000 patients, or the follow-up period reaches July 1, 2024, the study will be discontinued and outcomes by arm assessed. Trial enrollment will be ascertained using structured institutional data via an existing data feed from the Dana-Farber Enterprise Data Warehouse to the MatchMiner team. In our primary analysis, we will pool the two AI-assisted intervention arms and compare trial enrollment rates in the AI-assisted group (N~7600 total) to the standard process arm (N~3500) using a simple two-sample Z test of proportions. If the standard process arm enrollment rate remains ~ 7.5%, we would have 80% power given two-sided  $\alpha=0.05$  to detect an increase in enrollment rate to 9.1%. This would represent an operationally meaningful 21% relative increase in enrollment rates. We will take this approach rather than a time-to-event analysis, since traditional right censoring, in which patients are lost to follow-up but undetected events might have occurred after they were no longer followed, is not relevant for this outcome; we will have complete data on the outcome from DFCI (unascertained enrollment in a therapeutic trial would not be possible).

Comparison of the two intervention arms (Groups 2 and 3) to each other and to Group 1 will be a pre-specified secondary analysis. Additional pre-specified secondary outcomes will include whether patients have any consultations in the Center for Cancer Therapeutic Innovation and whether they consent to any therapeutic trial. Further pre-specified secondary outcomes will include trial consent and enrollment rates among patients who at any point during follow-up were ascertained as likely to change treatment in the next 30 days as defined by our algorithm; the proportion of new systemic therapy regimens that were clinical trials; and clinician opt-out rates. Of note, these are administrative/process outcomes, not clinical outcomes, such that our intervention does not itself constitute a clinical trial by the NIH definition. These endpoints will also be analyzed using the MatchMiner EDW data feed. Furthermore, the intervention consists of comparing ways to deliver information from the MatchMiner tool that is already accessible to treating clinicians, such that there is minimal risk to patients and clinicians.

The pilot phase work will be downsized when the interventional phase begins to minimize impact of the pilot on evaluation of the intervention. Specifically, the Breast Oncology Center and Thoracic Oncology Program components of the pilot will be discontinued, and the trials involved in the Center for Cancer Therapeutic Innovation (CCTI) pilot will be restricted to a subset of trials for rare patient populations for which CCTI collaborators determine there is a strong need to identify as many potential patients as possible. This list of trials will be determined at the time of intervention go-live, since it is challenging to predict trial portfolios far in advance.

This will be an interventional research study, but it will not itself constitute a clinical trial by the NIH definition, since the outcomes being measured (whether patients consent to or enroll on therapeutic clinical trials) are not themselves health-related outcomes for the patient.

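### The primary outcome and the 1000-patient closing count set no consent-date condition, so enrollments consented before go-live dilute the comparison; a consent-date rule is a cheap improvement

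*Protocol*

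**What the plan says.** All of this is in protocol section 9.0 unless noted.

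- **Cohort.** It is fixed at one date: "On the study go-live date, which is currently anticipated to be January 2, 2023", adjustable for technical reasons. It takes in every living adult with sequencing results and a tumor code outside the listed hematologic ones. Patients who have already consented to a trial are not excluded.
- **Randomization.** "Such patients will be randomly divided into three groups; randomization will be" at patient level.
- **Primary outcome.** "The primary study outcome will be whether patients enroll on any DFCI therapeutic" "clinical trial of an anti-cancer systemic therapy during the intervention follow-up period". The window is set by enrollment; consent date plays no part. Section 8.0 words the primary endpoint differently but also sets no consent-date condition.
- **Closing rule.** From December 2023, "enrollment events across all three study arms will be quantified every two months, without comparing enrollment among arms". The study ends by this rule: "Once total trial enrollment reaches 1000 patients, or the follow-up period reaches July 1, 2024".
- **Earlier trial participation.** The only restriction concerns trials on which the patient has already enrolled. It governs whether an email is sent, not whether an enrollment counts.
- **Consent.** It is a separate secondary outcome. Section 8.0 gives it as "rates of consent to any therapeutic clinical trial during that period", and section 9.0 takes it from the same institutional data feed.

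**The concern.** The intervention is an email that prompts an oncologist to consider a trial when the patient appears ready for one. On any go-live date some patients have signed consent and are not yet enrolled. When they enroll, they meet the primary outcome and add one to the closing count, in all three groups alike. The decision to join predates randomization, so these enrollments say little about what the emails achieve.

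Two things are at stake. The observed rate ratio is closer to 1 than the ratio among enrollments that the emails could have prompted. And the closing count, which the protocol keeps in order to secure power, is partly filled by events that carry little or no information on the intervention.

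**Working it through.** **Inputs from section 9.0.** Control rate 7.5%, AI-assisted rate 9.1%, two-sided alpha 0.05. Pooled AI-assisted group about 7600. Standard arm about 3500 in the power statement and about 3800 per group a little earlier; both are run here. In 2019 there were 890 enrollments from January 1 to November 30, which is 890/11 = 81 a month.

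**Assumed input.** The share of early enrollments whose consent predates go-live. The protocol gives no interval from consent to enrollment. A lag of 2 to 4 weeks at 81 a month gives about k = 40 to 80 such enrollments.

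**Formula.** Two-sample Z test with pooled variance under the null: power = Φ[(p2 − p1 − 1.96·s0)/s1], where s0 = √[p̄(1−p̄)(1/n1+1/n2)] and s1 = √[p1(1−p1)/n1 + p2(1−p2)/n2].

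**Step 1, the plan's own figure.** With n1 = 3500 and n2 = 7600: p̄ = 0.0860, s0 = 0.005726, s1 = 0.005541. Power = Φ[(0.016 − 0.01122)/0.005541] = Φ(0.862) = 80.6%. The stated 80% reproduces. With 3800 it is 82.8%. Events implied: 3500 × 0.075 + 7600 × 0.091 = 954, or 977 with 3800.

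**Step 2, dilution at exactly 1000 events.** The ratio 9.1/7.5 = 1.2133 is applied only to the 1000 − k enrollments consented after go-live. The k others are spread evenly:

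- b = k/(n1 + n2)
- q1 = (1000 − k)/(n1 + 1.2133·n2), q2 = 1.2133·q1
- observed rates p1 = q1 + b, p2 = q2 + b

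Worked case, 3800/7600 and k = 40: b = 40/11,400 = 0.00351; q1 = 960/13,021 = 0.07373; q2 = 0.08945; p1 = 0.07723; p2 = 0.09296; ratio 1.204. Then s0 = 0.005620, s1 = 0.005463, and power = Φ[(0.01573 − 0.01102)/0.005463] = Φ(0.863) = 80.6%.

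| Groups | k | Observed ratio | Power, counted | Power, excluded at the same close |
|---|---|---|---|---|
| 3800/7600 | 0 | 1.213 | 83.7% | 83.7% |
| 3800/7600 | 40 | 1.204 | 80.6% | 82.1% |
| 3800/7600 | 80 | 1.194 | 77.1% | 80.2% |
| 3500/7600 | 0 | 1.213 | 82.6% | 82.6% |
| 3500/7600 | 40 | 1.204 | 79.3% | 80.8% |
| 3500/7600 | 80 | 1.194 | 75.8% | 79.0% |

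Exclusion at the same closing date recovers about 1.5 to 3 points. Counting on to 1000 eligible enrollments restores the k = 0 rows. With a shorter lag, k = 20, the loss at 3800/7600 is about 1.5 points (83.7% to 82.2%).

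**Step 3, overshoot.** The count is taken every two months. At 81 a month from January 2, 2023 it stands near 81 × 11 = 891 in December 2023 and near 81 × 13 = 1053 in February 2024. At 1053 events with k = 40 or 80, power is 82.9% or 79.8% (3800/7600), and 81.7% or 78.5% (3500/7600).

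**The case against.** The strongest reply is that outcome, planning rate and power statement already agree with one another. The 2019 rate of 7.6% counts everyone who enrolled in the window, including anyone already in screening on January 1, 2019, and the 80% is stated for total rates of 7.5% and 9.1%. Power falls in the table only because the 21% increase is moved onto a subset of enrollments, which the protocol does not do. That stands. A reader might infer that the stated power is wrong, and the document does not support it. Nor does the claim rest on 1000 informative events: it implies 954 to 977 events in all, and overshoot of the count offsets part of any loss.

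It can also be said that many other enrollments owe nothing to an email, such as those of patients never flagged as ready, and that a consent-date rule removes only one slice. That is true. This slice, however, can be identified from information fixed before randomization, so removing it does not disturb the intention-to-treat comparison. The others depend on what happens afterwards.

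Three further inferences go too far.

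- That no email could have influenced these enrollments. A consented patient who is not yet enrolled may still trigger an email, which could bear on completing enrollment or on another trial. Only the earlier consent is beyond its reach.
- That the consent and enrollment endpoints contradict each other. They are different events, and any calendar window cuts between sequential events.
- That a screening scan always falls between consent and enrollment. The protocol does not say so.

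Finally, a counting rule of this kind could sit in an analysis plan that is not at hand. That is a reason to treat the point as an improvement rather than an error.

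**Conclusion.** The point holds as a cheap improvement to the outcome definition. As worded, enrollments on consents signed before go-live are primary events and count toward closing. They are balanced by randomization, so there is no bias and no inflation of type I error. The cost is a diluted ratio, 1.204 to 1.194 in place of 1.213, and about 3 to 7 points of power at 1000 events. Those figures rest on an assumed lag of 2 to 4 weeks, the 2019 monthly rate, and the assumption that the 21% increase applies only to enrollments consented after go-live. If the 21% is instead read as the net increase over all enrollments, the stated power stands, but the emails must then produce more than 21% among the enrollments they can prompt.

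**What to change.** In section 9.0, define the primary event as the first enrollment on a DFCI therapeutic trial of systemic anti-cancer therapy with consent dated on or after go-live. Apply the same rule to the 1000-patient closing count. Keep every randomized patient in the denominator, including those with an open consent at go-live. Report the all-enrollment result as a sensitivity analysis, and show enrollments with earlier consent by arm.

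The text change is a sentence or two. It needs the data feed to link each enrollment to its own consent date. The protocol says that consent outcomes come from that feed but does not confirm the link, so this should be checked first. Reaching 1000 eligible enrollments may take about two to four weeks longer, subject to the two-monthly counts and the July 1, 2024 limit.

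### The primary Z test is valid and powered as stated, but it leaves out baseline variables likely to predict enrollment and so gives up a modest, nearly free gain in precision.

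*Protocol*

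**What the plan says.** Section 9.0 of the Protocol fixes the primary analysis itself. Groups 2 and 3 are pooled, and the plan is to "compare trial enrollment rates in the AI-assisted group (N~7600 total") "to the standard process arm (N~3500") "using a simple two-sample Z test of proportions". No covariates enter. The section gives a reason for not using a time-to-event analysis, but none for leaving out baseline adjustment.

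Randomization is by patient. Stratified randomization will "not be performed, due to the large sample size and heterogeneity in treating disease" centers, clinicians and cancer types. The primary analysis is by intention to treat.

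On the available data:

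- Eligibility in Section 9.0 uses the OncoTree code. The readiness rule uses the predicted probability of treatment change, and MatchMiner matches to trials the patient has not already joined.
- Section 8.0 lists enrollment in therapeutic trials among the outcomes for model training.
- Section 7.0 plans an evaluation of how well the models predict consent and enrollment, but the Protocol reports no result.

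**The concern.** Heterogeneity across cancer types, centers and clinicians is given as a reason not to stratify, and the analysis then makes no use of it either. The premise of the study is that record-based predictions help to show who may be ready for a trial. Values of those predictions from before go-live are therefore natural covariates for an enrollment outcome.

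The stated power leaves almost no margin over 80% for a difference of 1.6 percentage points. Adjusting for pre-randomization predictors would narrow the interval for that same difference without more patients or longer follow-up. At stake are a few points of power and a somewhat shorter interval. Bias is not at issue.

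**Working it through.** **Inputs from Section 9.0.** n1 = 3500 (standard arm), n2 = 7600 (pooled AI arms), p1 = 7.5%, p2 = 9.1%, two-sided alpha 0.05. The control rate ("If the standard process arm enrollment rate remains ~ 7.5"%) agrees closely with the 2019 figure of 890/11,650 = 7.6%.

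**Input not in the documents.** R², the share of outcome variance explained by baseline covariates. A range is assumed.

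**Step 1: reproduce the stated power.**

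- d = 0.091 − 0.075 = 0.016
- Pooled rate = (3500 × 0.075 + 7600 × 0.091)/11,100 = 954.1/11,100 = 0.0860
- s0 (pooled SE) = √[0.0860 × 0.9140 × (1/3500 + 1/7600)] = 0.00573
- s1 (unpooled SE) = √[0.075 × 0.925/3500 + 0.091 × 0.909/7600] = 0.00554
- Formula A, pooled SE throughout: Φ(d/s0 − 1.96) = Φ(0.834) = 79.8%
- Formula B, pooled SE under the null and unpooled under the alternative: Φ((d − 1.96 s0)/s1) = 80.6%

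The Protocol's 80% is right. By formula B, the rate detectable with 80% power is 9.09%, in line with the stated 9.1%.

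**Step 2: relate predictive strength to R².** Under a logistic-normal risk model with an overall rate of 8.6%, an AUC of about 0.64, 0.70, 0.75 or 0.79 corresponds to R² of about 0.02, 0.05, 0.08 or 0.12. With an outcome this uncommon, even a fair discriminator explains little variance.

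**Step 3: power with adjustment.** Both standard errors are multiplied by √(1 − R²). The equivalent gain in sample size is 1/(1 − R²) − 1, applied to N = 3500 + 7600 = 11,100.

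| Assumed R² | Power, A | Power, B | Equivalent gain | Extra patients |
|---|---|---|---|---|
| 0 | 79.8% | 80.6% | none | 0 |
| 0.02 | 80.6% | 81.4% | 2.0% | 227 |
| 0.05 | 81.8% | 82.6% | 5.3% | 584 |
| 0.08 | 83.0% | 83.8% | 8.7% | 965 |
| 0.12 | 84.6% | 85.4% | 13.6% | 1,514 |

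By formula B, the detectable rate moves from 9.09% to 9.05% at R² 0.05 and to 9.02% at R² 0.08, a shift of less than 0.1 percentage point.

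**The case against.** The strongest reply is that nothing here is wrong. Under patient-level randomization the Z test is unbiased and holds its level, and its power is stated correctly. With about 11,000 patients, chance imbalance is small, and the Protocol gives sample size as its first reason for not stratifying. All of this stands.

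The predictive strength is also unknown. A reader might infer that strong predictors are being discarded, but the Protocol gives no AUC, R² or association with enrollment. The model score may be weak for this purpose, since Section 9.0 describes a 30-day horizon while enrollment is counted over a follow-up that could run to July 1, 2024. At R² 0.02 the gain is under one point.

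A reader might also assume that every randomized patient has every covariate. The text does not support that. Scores arise when an imaging report is generated, and the sequenced cohort includes patients not actively followed at the center. No stored match count at go-live is described.

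Finally, power has other sources. Follow-up continues until 1,000 enrollments or the calendar limit, and the design scenario itself implies only about 954. Section 9.0 also says "since 2019, we will therefore have approximately 3800 patients in each group who have" imaging in the intervention period. With 3800 controls instead of 3500, unadjusted power is already 82.1% (A) or 82.8% (B). That discrepancy needs reconciling separately.

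These points limit the size of the gain. They do not remove the case for adjustment: at this sample size, with close to 1,000 events, a few prespecified baseline covariates would not be expected to cost precision even if they predict weakly. The choice of primary test is made in the Protocol, so it is not a detail left to the SAP.

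**Conclusion.** The point holds as a recommendation on efficiency. The primary test is valid and correctly powered, but it forgoes a likely gain of about 1 to 5 power points, equivalent to roughly 2% to 14% more patients.

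The size rests on three assumptions: R² between 0.02 and 0.12, the 3500 and 7600 of the power statement as the analyzed numbers, and covariates available for most patients. None of the documents' own figures settles R². If every randomized patient is analyzed, including those with no imaging in the period, R² could differ, and the Protocol gives no basis for saying by how much.

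It would be wrong to conclude that the trial is underpowered as designed, or that the lack of stratification is a flaw. With patients randomized individually and this many of them, stratification adds almost nothing once covariates are adjusted for in the analysis.

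**What to change.** Make the primary analysis a prespecified logistic regression on arm (pooled AI vs standard) and a few covariates taken as of go-live:

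- cancer type, grouped from the OncoTree code;
- prior therapeutic-trial enrollment (yes/no);
- the last predicted probability of treatment change before go-live, with a separate category for patients with no score or no recent imaging;
- the number of MatchMiner matches, if a go-live snapshot can be taken.

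Standardize the fitted model over the analysis set to give the same risk difference that the Z test targets, with a robust confidence interval. Use no score or imaging from after go-live as a covariate, because these follow randomization. Fix the covariates and their coding before outcomes by arm are assessed. Keep the unadjusted Z test as a sensitivity analysis.

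The cost is a baseline snapshot from existing feeds, a rule for missing scores, a few lines of code, and a primary test that is slightly less simple to explain. No extra patients or follow-up are needed.
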